## Abstract

**Background:**

Back and neck disability are frequent in older adults resulting in loss of function and independence. Exercise therapy and manual therapy, like spinal manipulative therapy (SMT), have evidence of short and intermediate term effectiveness for spinal disability in the general population and growing evidence in older adults. For older populations experiencing chronic spinal conditions, long term management may be more appropriate to maintain improvement and minimize the impact of future exacerbations. Research is limited comparing short courses of treatment to long term management of spinal disability.

The primary aim is to compare the relative effectiveness of 12 weeks versus 36 weeks of SMT and supervised rehabilitative exercise (SRE) in older adults with back and neck disability.

**Methods/Design:**

Randomized, mixed-methods, comparative effectiveness trial conducted at a university-affiliated research clinic in the Minneapolis/St. Paul, Minnesota metropolitan area.

**Participants:**

Independently ambulatory community dwelling adults ≥ 65 years of age with back and neck disability of minimum 12 weeks duration (n = 200).

**Interventions:**

12 weeks SMT + SRE or 36 weeks SMT + SRE.

**Randomization:**

Blocked 1:1 allocation; computer generated scheme, concealed in sequentially numbered, opaque, sealed envelopes.

**Blinding:**

Functional outcome examiners are blinded to treatment allocation; physical nature of the treatments prevents blinding of participants and providers to treatment assignment.

**Primary endpoint:**

36 weeks post-randomization.

**Data collection:**

Self-report questionnaires administered at 2 baseline visits and 4, 12, 24, 36, 52, and 78 weeks post-randomization. Primary outcomes include back and neck disability, measured by the Oswestry Disability Index and Neck Disability Index. Secondary outcomes include pain, general health status, improvement, self-efficacy, kinesiophobia, satisfaction, and medication use. Functional outcome assessment occurs at baseline and week 37 for hand grip strength, short physical performance battery, and accelerometry. Individual qualitative interviews are conducted when treatment ends. Data on expectations, falls, side effects, and adverse events are systematically collected.

**Primary analysis:**

Linear mixed-model method for repeated measures to test for between-group differences with baseline values as covariates.

**Discussion:**

Treatments that address the management of spinal disability in older adults may have far reaching implications for patient outcomes, clinical guidelines, and healthcare policy.

**Trial registry:**

www.ClinicalTrials.gov; Identifier: NCT01057706.

## Background

Musculoskeletal complaints such as back and neck pain are common in the general population but are particularly troublesome in older adults [[1]] and into extreme old age [[2]]. In a one to three month time period, approximately 20-35% of older adults report low back pain [[3]–[6]], 5-22% report neck pain [[4]–[6]], and 9-11% suffer concurrent low back and neck pain [[5],[6]]. Chronic musculoskeletal pain and disability are often associated with increased dependence [[1]], decreased physical functioning [[1],[6],[7]], and other co-morbidities [[6],[8]], which can inhibit vital social activities and quality of life [[7]], as well as contribute independently to mortality [[9]]. Healthcare expenditures for back and neck problems have increased with limited improvement in health status [[10],[11]]. A Medicare claims analysis found back pain to be the second most costly chronic non-cancer pain condition; the adjusted cost attributed to back pain per affected member was $2888 annually [[12]]. With nearly 40 million older adults living in the US [[13]], this quickly growing age group [[14]] is projected to double by 2040 [[13]]. Subsequently, investigating conservative non-pharmacological treatments that temper the effects of back and neck problems is an important public health issue [[12]].

In the general population, exercise therapy has demonstrated effectiveness for back and neck pain and disability [[15],[16]], particularly when tailored to the individual. Evidence suggests that older adults who exercise experience reduced risk of disability and functional decline [[17]]. Accordingly, regular exercise is recommended to maintain health and functional ability among older adults [[18]]. Importantly, Hayden et al. found exercise combined with conservative treatment such as manual therapy improved functional outcomes in the general population with chronic low back pain [[15]].

Approximately 11–17% of older Americans seek care from chiropractors annually [[19],[20]]. While a majority of research has focused on short and intermediate term effectiveness of spinal manipulative therapy (SMT) in the general population [[16],[21]], there is a limited, yet growing body of evidence suggesting effectiveness of SMT for back-related disability in older adults [[22],[23]]. Considering that back and neck pain are often chronic in nature and part of a constellation of co-morbidities that impact functional ability [[24]], a long term management approach may be more appropriate to effectively address back and neck disability in older adults. Long term management may aid in maintaining the improvement in functional capacity achieved during a short course of treatment [[25]] and may minimize the impact of future exacerbations [[26]]. This theory is supported by a small study showing that nine months of continued treatment with SMT sustained participants’ improvement in low back pain and disability compared to those receiving only one month of SMT [[27]]; however, the effectiveness of long term management of back and neck disability in older adults has yet to be investigated in a full scale trial [[28]].

### Aims

The primary aim is to compare the effectiveness of 12 versus 36 weeks spinal manipulative therapy and supervised rehabilitative exercise (SMT + SRE) by assessing change in the Neck Disability Index (NDI) and Oswestry Disability Index (ODI) at 36 weeks.

Four secondary aims assess between-group differences in:

1) secondary patient-rated outcome measures at week 36 at 78, including disability at week 78

2) functional outcomes at week 37

3) patients’ perceptions of treatment

4) cost effectiveness and cost utility at weeks 36, 52, and 78. This aim will be described and reported elsewhere.

## Methods/Design

Ethical approval from Northwestern Health Sciences University’s (NWHSU) institutional review board (IRB) was received in October 2009.

### Design & setting

This randomized, observer-blinded, comparative effectiveness trial is being conducted at the Wolfe-Harris Center for Clinical Studies at NWHSU in Bloomington, Minnesota. Notice of privacy practices and written informed consent are secured from all subjects prior to participation.

### Methodological changes to study protocol

The initial study protocol was a three-arm trial, which included a minimal-intervention comparison group of SRE alone for 36 weeks. Slower than projected enrollment and award reductions from the funding agency prompted changes to the study protocol 18 months after recruitment began. A modified study design was proposed by study investigators and approved by the steering committee, funding agency, IRB, and data and safety monitoring board (DSMB). The initial design, modified design, and rationales for each change are described in Table 1. The following three secondary aims were added to use the data collected from those already randomized to the SRE alone group:

**Table 1 T1:** Differences between the initial and modified trial designs and precipitating reasons for the change

**Initial design**	**Modified design**	**Rationale**
Three-arm trial (n = 300)	two-arm trial (n = 200)	Enrollment
• 36 weeks SMT + SRE (n = 88)	• 36 weeks SMT + SRE (n = 100)	Funding
• 12 weeks SMT + SRE (n = 124)	• 12 weeks SMT + SRE (n = 100)	
• 36 weeks SRE alone (n = 88)		
n = 300	n = 200 (for primary and secondary aims 1–4)	Enrollment
	n = 18 (for additional secondary aims A-C)	Funding
Randomization ratio 1:1.4:1	Final randomization ratio 1:1	Enrollment
		Funding
Pertinent inclusion/exclusion criteria:	Pertinent inclusion/exclusion criteria:	Enrollment
• NDI and ODI ≥ 15% each at both baseline evaluations	• NDI and ODI ≥ 10% each *AND* combined score of ≥ 25% at first baseline evaluation only	
Functional outcomes:	Functional outcomes:	Funding
• short physical performance battery		
• hand grip strength		
• accelerometry	• short physical performance battery	
• postural sway	• hand grip strength	
• range of motion	• accelerometry	
• static endurance		

A) assess within group change for all patient-rated outcomes at weeks 36 and 78

B) assess within group change for functional outcomes at week 37

C) describe participants’ perceptions of treatment

The remainder of this manuscript describes the methodology for the modified trial.

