### Randomization

Restricted randomization employs a 1:1 allocation ratio. The randomization scheme was generated by an independent statistician using randomly permuted block sizes created with a computerized random number generator. As participants become eligible for randomization, sequentially numbered, opaque, sealed envelopes containing treatment assignments are drawn and opened by study staff in the participant’s presence. The randomization scheme and block sizes are concealed from all study staff including those who take part in eligibility determination, enrollment, and randomization.

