### Primary and secondary analyses

Primary analysis will use a linear mixed-model method for repeated data to test for between-group differences in neck and back disability separately at week 36, with baseline variables that may influence outcomes as covariates [[82],[83]]. Secondary analysis of disability will include testing for between-group differences at weeks 4, 12, 24, 52, and 78, as well as within-group change at all time points. Longitudinal analysis will be performed through the short (weeks 4, 12, 24 and 36) and long term (weeks 4, 12, 24, 36, 52 and 78).

Secondary outcome measures, including pain, general health, improvement, self-efficacy, kinesiophobia, satisfaction, medication use, and functional outcome measures will be similarly calculated for within- and between-group differences. This study is not powered to detect change in the secondary outcome measures.

Content analysis of qualitative interviews will use both inductive and deductive approaches [[84]] to identify themes that occur in response to questions asked [[85]]. When coding is complete, frequency of themes will be quantified and representative quotations will be identified [[85],[86]].

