### Trial status and timeline

Recruitment began in January 2010 and was completed in May 2013; participants received treatment through December 2013. Data collection will continue through 2014 which will be followed by data cleaning, analysis, and reporting in 2015.

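### Allocation ratio and entry thresholds changed mid-recruitment, but the primary model names no term for design stage; the likely bias is small and almost free to remove

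*Protocol article*

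**What the plan says.** The section on methodological changes reports that slow enrolment and funding cuts "prompted changes to the study protocol 18 months after recruitment began". The trial status section adds: "Recruitment began in January 2010 and was completed in May 2013". The change therefore falls around mid-2011, well inside the recruitment period.

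Table 1 shows two changes that matter here:

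- **Allocation.** The initial design had "Randomization ratio 1:1.4:1" across 36-week SMT + SRE, 12-week SMT + SRE and SRE alone (planned 88, 124 and 88). The modified design has two arms of 100 and "Final randomization ratio 1:1".
- **Entry thresholds.** The initial rule was "NDI and ODI ≥ 15% each at both baseline evaluations". The modified rule is at least 10% on each index plus a combined score of at least 25%, at the first baseline visit only.

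Table 1 assigns 200 patients to the primary aim and secondary aims 1 to 4. It sets apart only the 18 exercise-alone patients, for the added within-group aims.

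The Randomization section states: "Restricted randomization employs a 1:1 allocation ratio". The primary analysis is a linear mixed model to "test for between-group differences in neck and back disability separately at week 36", with baseline values and other influential baseline variables as covariates. Under Statistical methods, further covariates are demographic or clinical variables that the investigators judge relevant or that reach a correlation of 0.5. Design stage is not named in any of these places.

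**The concern.** Within each stage, randomisation makes the arms comparable. Across the pooled 200 it does so only if the allocation probability was constant or the analysis conditions on stage. Here a patient entering before the change had a lower chance of the 36-week arm than one entering after it, and was also selected under stricter disability criteria. Early patients are therefore somewhat over-represented in the 12-week arm.

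If early and late patients differ at week 36 in a way that the baseline covariates do not capture, such as calendar time or a different mix of recruits, part of that difference is credited to treatment. Both indices were used jointly to select patients but are analysed separately, so adjusting one index for its own baseline need not remove selection on the other.

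**Working it through.** **Inputs from the protocol article.** Initial ratio 1:1.4:1; 18 patients in the exercise-alone arm; 200 in the primary aim; target difference 10 points on the ODI; 85 evaluable patients per group at power 0.90 and alpha 0.025; 15% dropout.

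**The plan's own figures.**
- 124/88 = 1.41 and 88 + 124 + 88 = 300, as stated.
- Reading the 0.20 as an SD and alpha as one-sided, n = 2 × [0.20 × (1.960 + 1.282)/0.10]² ≈ 84.1, so 85 per group, and 85/0.85 = 100. An SD of 20 points is used below on that reading.

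**Stage-1 size (assumption).** The article does not give the per-arm numbers before the change. With 18 in the exercise-alone arm, the ratio implies about 18 in the 36-week arm and 18 × 1.4 = 25.2, about 25, in the 12-week arm. That is 43 of 200 (22%), leaving 157 for stage 2.

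**Stage-1 share by arm, under two readings of the final 1:1.**

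| Reading | Stage 2 (36 wk : 12 wk) | Totals | Stage-1 share, 36 wk | Stage-1 share, 12 wk | Difference |
|---|---|---|---|---|---|
| A: overall end ratio | 82 : 75 | 100 : 100 | 18% | 25% | 7.0 points |
| B: post-change ratio | 78.5 : 78.5 | 96.5 : 103.5 | 18.7% | 24.2% | 5.5 points |

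Under A, stage 2 must favour the 36-week arm (82/75 = 1.09). Under B, the totals miss 100 per arm slightly.

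**Bias if stage is omitted.** Bias = (stage-1 share in the 12-week arm − stage-1 share in the 36-week arm) × g, where g is the stage difference in week-36 ODI at equal baseline. The article gives no value for g, so a range is shown.

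| g (ODI points) | Bias, A | Bias, B |
|---|---|---|
| 2 | 0.14 | 0.11 |
| 5 | 0.35 | 0.28 |
| 10 | 0.70 | 0.55 |
| 15 | 1.05 | 0.83 |

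A 1-point bias needs g = 1/0.07 ≈ 14 (A) or 1/0.055 ≈ 18 (B).

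**Sensitivity to stage-1 size, at 100 per arm.** With 12 and 17 patients the difference in share is 5 points and the bias is 0.25 (g = 5) to 0.5 (g = 10). With 36 and 50 it is 14 points, and 0.7 to 1.4.

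**Against sampling error.** The SE of the arm difference is about 20 × √(2/85) = 3.1 points. A bias of 0.35 is about 0.11 SE, and 0.70 is about 0.23 SE.

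**Would the stated covariate rule bring stage in?** With a stage-1 share of 0.215, the SD of the stage indicator is √(0.215 × 0.785) = 0.41. A correlation of 0.5 with an outcome of SD 20 needs a gap of 0.5 × 20/0.41 ≈ 24 points; a 5-point gap gives r ≈ 0.10. Stage would enter only at the investigators' discretion.

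**Cost of a stage term.** Under A, the arm–stage correlation is (25 × 82 − 18 × 75)/√(100 × 100 × 43 × 157) = 0.085, so the variance inflation is 1/(1 − 0.085²) = 1.007. Under B, r = 0.067 and the inflation is 1.005. Power at 85 per group stays at 0.90.

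**The case against.** The strongest reply has four parts.

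1. **The Randomization section is not wrong.** The section on methodological changes ends by limiting the rest of the article to the modified trial, and Table 1 already prints both ratios. A reader might infer that the single 1:1 statement misreports the allocation. The article does not support that, and this part of the reply stands in full.
2. **Pooling is nowhere stated, and the covariate set is open.** Both are true. The SAP is not shown and may include stage. But nothing sets aside early patients in the two retained arms, whereas the 18 exercise-alone patients are set aside explicitly. The stated covariate rule covers demographic and clinical variables; stage is neither, and it would hardly ever reach a correlation of 0.5. A factor that determined the allocation probability belongs in the model by design.
3. **The severity shift is mostly handled.** Selection was on baseline NDI and ODI, and the model adjusts for baseline values averaged over two visits. This largely stands. Only a stage difference at equal baseline can bias the result, and the article contains no evidence on whether one exists or in which direction.
4. **The effect is minor.** It also stands that a bias of about 0.1 to 0.2 SE would not create or hide a 10-point effect. A reader might infer from the mid-trial change that arm and stage are seriously confounded. They are not: randomisation holds within each stage, and the estimated imbalance is 5.5 to 7 percentage points.

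**Conclusion.** The point holds as a modest one. Allocation probability and entry criteria changed in the same mid-recruitment modification, and the described primary model has no term for it. The pooled comparison is therefore not strictly the within-stage randomised comparison. The plausible bias is about 0.3 to 0.7 ODI points for a residual stage gap of 5 to 10 points, and up to 1.4 if stage 1 was twice as large as estimated, against a target of 10.

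This rests on three assumptions: that the 200 include early patients in the two retained arms; that stage-1 numbers follow from the 18 exercise-alone patients at 1:1.4:1; and that some stage difference remains after baseline adjustment. If early patients are not among the 200, the concern disappears. The case for acting is that the remedy costs almost nothing, not that the result is in danger.

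**What to change.** - Include design stage (randomised before or after the modification) as a fixed effect in the primary model and in all other between-group models.
- State whether the final 1:1 in Table 1 is the ratio used after the change or the overall end ratio.
- When results are reported, give the number randomised to each arm before and after the change.

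The cost is one degree of freedom and one sentence in the analysis plan. Variance inflation is about 1.005 to 1.007, power is unchanged at 0.90, and the sample size stays at 200. Stage should be recoverable from the randomisation records, and the article schedules analysis for 2015, after data collection ends. No change to the Randomization section is needed.

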### Participants

This study will enroll 200 older adults who report functional disability in the back and neck regions. See Figure 1 for participant flow through the study.

**Figure 1 F1:**
[figure not shown]
Participant flow.

### Recruitment strategy

Participants from the Minneapolis/St. Paul metropolitan area are recruited through targeted mailing of brochures, church bulletins, movie theater advertisements, distributed flyers and posters, informational presentations, letters to physicians, and online strategies such as the NWHSU’s website, Craigslist®, and Facebook®.

### Inclusion/exclusion criteria

To be eligible, participants need to be 65 years of age or older with self-reported back and neck disability.

Inclusion criteria are:

• Back and neck disability of ≥ 12 weeks duration

• Back and neck disability, defined as

◦ 10% or higher on Neck Disability Index (NDI),

◦ 10% or higher on Oswestry Disability Index (ODI), and

◦ A combined score (NDI + ODI) of at least 25%

• Stable pain medication plan 4 weeks prior to baseline

• Ability to read and speak English

• Community dwelling

• Ability to ambulate without the aid of a wheelchair or motorized scooter

Exclusion criteria are:

• Surgical spinal fusion [[29]]

• Multiple incidents of spinal surgery [[29]]

• Spinal surgery in the last 6 months

• Ongoing non-pharmacological treatment for a spinal condition

• Less than 25 on the Folstein Mini-Mental State Examination [[30],[31]]

• Untreated or unstable clinical depression screened by the Geriatric Depression Scale [[32]–[34]]

• Current or pending financial compensation for a neck or back condition [[35],[36]]

• Co-morbid conditions

◦ Ongoing substance abuse

◦ Body mass index ≥ 40

◦ Stage III or IV cancer diagnosis in the past 5 years or active cancer treatment

◦ Uncontrolled hypertension

◦ Advanced Parkinson’s Disease

◦ Advanced multiple sclerosis

◦ Uncontrolled metabolic disease

◦ Diffuse idiopathic skeletal hyperostosis

• Contraindication to SMT

◦ Advanced spinal stenosis [[37]]

◦ Spinal fracture [[37]]

◦ Stroke or transient ischemic attack

◦ Inflammatory or destructive tissue changes of spine

◦ Bleeding disorder [[38]]

◦ Severe osteoporosis [[38]]

◦ Progressive neurological deficits or cauda equina syndrome [[38]]

• Contraindication to SRE

◦ Advanced cardiovascular or pulmonary disease [[39]]

### Eligibility determination

#### Phone screen

Certified study personnel administer a computer-guided questionnaire to interested individuals by phone. Responses are directly entered into a computer program that determines general eligibility for the first baseline evaluation. Baseline evaluation consists of two visits, 7–21 days apart, which serve as a compliance check and provide a more accurate baseline estimate.

#### First baseline evaluation

The first baseline evaluation includes informed consent, cognitive function assessment, self-report questionnaire including demographic and outcome measures, and a history and examination by a licensed clinician. The physical examination focuses on the cervical and lumbar spine and assesses posture, gait, range of motion, orthopedic and neurologic tests. Unless recent imaging is available, cervical and lumbar plain radiographs and bone mineral density scans of the distal radius and ulna are taken to rule out exclusionary co-morbidities and contraindications (e.g., spinal stenosis, osteoporosis). Potential participants that qualify at the first baseline evaluation are reviewed by a group of clinicians and investigators who reach consensus on eligibility (qualify, does not qualify, or referral if necessary).

#### Second baseline evaluation

A second baseline evaluation includes an informed consent (i.e., review of study activities), a self-report questionnaire, and functional outcome assessment. Consenting participants are then randomly allocated by staff masked to upcoming treatment assignment.

### Randomization

Restricted randomization employs a 1:1 allocation ratio. The randomization scheme was generated by an independent statistician using randomly permuted block sizes created with a computerized random number generator. As participants become eligible for randomization, sequentially numbered, opaque, sealed envelopes containing treatment assignments are drawn and opened by study staff in the participant’s presence. The randomization scheme and block sizes are concealed from all study staff including those who take part in eligibility determination, enrollment, and randomization.

